#### Exclusion Criteria

Exclusion criteria are as follows: (1) individuals who disclose a past or present self-reported diagnosis of bipolar disorder, borderline personality disorder, obsessive-compulsive disorder, schizophrenia, or a substance abuse or addiction in the past 3 months; and (2) individuals who disclose having suicidal ideation or who have attempted suicide in the past 6 months prior to the study.

### Recruitment Plan

Participants will be recruited from a web-based platform (CloudResearch) [40]. Potentially eligible participants will be prescreened and eligibility assessed. After eligibility screening, they will be invited to a Zoom meeting where the study investigator further explains the study procedures. If the participant is interested, written consent will be obtained prior to randomization. The investigator will perform electronic randomization, with study IDs blindly assigned to experimental and control group participants. Study ID information will be recorded on an excel sheet as well as on the SurveyMonkey platform. After a participant completes baseline questionnaires, blinded research assistants will play a taped version of the video assigned to the participant in accordance with the randomization plan.

The randomly assigned participants will proceed to watch a 15-minute guided video of either FT-EMDR (experimental condition) or S-EMDR (comparison condition) in a quiet environment. Assessments will take place at pre- and postintervention and 1-month follow-up.

A streaming recruitment method will be employed where the study description is made available on the internet (CloudResearch platform) for a duration of 15 minutes prior to a participation-designated interview time slot. This will enable potential participants to enter the study description link, read a description of the study format, and pass the eligibility criteria before proceeding further if interested in study participation.

The additional steps to “streaming recruitment” require specifying how many participants can access the experiment’s Zoom link at a given time, up to a maximum of 15. When more than one subject uses the link to enter the Zoom waiting room, the researcher will allow the first participant to enter the Zoom study meeting, while the remaining waiting room occupants are thanked for their interest and prompted to sign off. Once 1 eligible participant enters the video interview, the Zoom meeting will be locked, and no additional participants can access or join.

### Procedure

This study will require 2 contact commitments from participants during a 4-week period. The first interaction will include gaining consent, completing preintervention psychometric questionnaires, and then watching and engaging in the 15-minute either intervention or control video. Subsequently, participants will complete postintervention measures and are provided with a debriefing statement.

The second interaction will be a follow-up of intervention outcomes 1 month after the initial interaction. A SurveyMonkey link will be sent out to participants via the CloudResearch platform, which will include all primary and secondary outcome measures. Both participants and research assistants will be blinded to experimental and control conditions throughout the trial.

### Interventions

#### Experimental Group

After a participant consents and completes demographic and baseline psychometric questionnaires, a “blinded” research assistant will share the computer screen and play a taped video of FT-EMDR containing vocalized and viewable instructions by licensed EMDR practitioners. Participants will be asked to follow the instructions with their full attention in a distraction-free environment. Participants assigned to the experimental condition will be invited by the video instructor to perform the following additional tasks: (1) identify a traumatic memory and rate its disturbance on a numerical scale that extends from 0 (no disturbance at all) to 10 (most disturbing)—This is often referred to as the Subjective Units of Distress Scale (SUDS) [41]; (2) identify a PEF, which can include a person, vacation, pet, favorite activity, or favorite music that is immediately gratifying when recalled or is a reminder of a past gratifying experience; (3) rhythmically tap knees while thinking of the selected PEF; periodically, the video instructor will say the word “flash,” prompting 4-6 rapid blinks of the eyes, simultaneously establishing the blink rhythm and duration; (4) continuously envision the proposed PEF after blinking; and (5) respond to periodic check-ins concerning changes in the memory experience.

At the end of the video, the instructor will ask participants to rate their target memory once again on the SUDS. The assigned research assistant will collect SUDS reports at baseline and postintervention.

The PEF is considered essential to the FT-EMDR approach component. Participants will be instructed to immerse themselves into their PEF while rhythmically tapping their knees; however, they will not be instructed to avoid and suppress their target memory. Conversely, participants will be encouraged to bring their attention back to their PEF once distracted by the target memory.

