**Methods:**

This double-blinded, web-based, 2-arm randomized controlled trial will employ self-report outcomes. A total of 90 participants will be identified from the web-based CloudResearch platform and randomly allocated to the experimental or comparison group. Inclusion criteria are as follows: (1) approved for engagement by the CloudResearch platform; (2) 25-60 years of age; (3) residing in Canada or the United States; (4) a recalled disturbing memory of an event >2 years ago that has not repeated and was moderately or more upsetting during occurrence; (5) memory moderately or more upsetting at baseline and not linked to an earlier memory that is equally or more than equally disturbing. Exclusion criteria are bipolar disorder, borderline personality disorder, obsessive-compulsive disorder, schizophrenia, substance abuse or addiction in the past 3 months, suicidal ideation, and suicide attempt in the past 6 months. Interventions include guided video instruction of full FT or guided video of EMDR. Outcome measures are as follows: Primary outcome is PTSD symptoms that are measured by the PTSD Checklist for DSM-5 (Diagnostic and Statistical Manual of Mental Disorders-5) at 1-month follow-up. Secondary outcomes are State Anxiety subscale of State-Trait Anxiety Inventory at baseline, postintervention, and 1-month follow-up; Trait Anxiety subscale of State-Trait Anxiety Inventory; depression (Patient Health Questionnaire-9); and Positive and Negative Affect Schedule measured at 1-month follow-up.

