## Methods

### Overview

Previous studies of FT-EMDR have indicated that guided in-person FT effectively reduces subjective units of distress caused by distressing memories. These studies were limited due to a lack of randomization and adequate control comparison. This study will be an assessor-blinded, 2-arm (experimental and control) randomized controlled trial, which minimizes placebo effects and implements an adequate sample size and psychometric measurement. This study is expected to have an overall duration of 3 months. The length of study for each participant will be 4 weeks. The recruitment period is estimated to last for 2 months.

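### The procedures contradict the stated blinding of research assistants, and a session-1 debriefing of unstated content puts participant masking at risk before the self-reported primary outcome

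*Protocol article*

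**What the plan says.** The title, abstract, Introduction and Discussion of the protocol article call the trial double-blinded; the abstract's wording is "This double-blinded, web-based, 2-arm randomized controlled trial will employ self-report outcomes". Methods, Overview uses a different label and attaches a benefit to it: "This study will be an assessor-blinded, 2-arm (experimental and control) randomized controlled trial, which minimizes placebo effects". Procedure says who is masked and for how long: "Both participants and research assistants will be blinded to experimental and control conditions throughout the trial".

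The delivery steps are as follows. In Recruitment Plan, "blinded research assistants will play a taped version of the video assigned to the participant in accordance with the randomization plan". In Experimental Group, the "research assistant will share the computer screen and play a taped video of FT-EMDR containing vocalized and viewable instructions", and later "The assigned research assistant will collect SUDS reports at baseline and postintervention". Comparison Group says that the PEF is not mentioned in the comparison video and that participants there attend only to the traumatic memory.

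At the end of the first contact, "participants will complete postintervention measures and are provided with a debriefing statement". What that statement contains is not described. The PCL-5 follows 1 month later through a SurveyMonkey link that the participant completes.

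**The concern.** Two questions arise. First, can a person who plays the allocated video on a shared screen be unaware of which video it is? If not, the article claims a design property that its own steps do not deliver.

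Second, does participant masking last until the outcome that matters? Every outcome is a self-report, and the Discussion names sole reliance on self-report as a limitation. The participant is thus the assessor, and masking the participant is the blinding that bears directly on the PCL-5. The article leans on it: the Discussion faults two earlier web-based studies because their post-treatment assessments were unblinded and open to placebo response, and it offers the double-blinded design as the remedy. If participants learned before month 1 that they had received the new or the comparison video, their expectations could move the PCL-5, S-STAI and PHQ-9 in the hypothesised direction.

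**Working it through.** No figure is at issue, so the check sets the article's sections side by side.

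**1. Is the assistant masked?**
- Claim (Procedure): assistants are blinded to condition throughout.
- Steps (Recruitment Plan, Experimental Group): the assistant shares the screen and plays the assigned video, whose instructions can be heard and seen.
- Are the videos distinguishable? Yes. The experimental video asks for a PEF and keeps returning to it. The comparison video never mentions it and directs attention only to the trauma.
- The article describes no arrangement that would keep the assistant from seeing or hearing the video.

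The claim and the steps cannot both hold. At most the assistant might not know which video is the favoured one, and the article does not describe masking of that kind.

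**2. Which SUDS ratings are affected?**
- In Experimental Group, the first SUDS rating is task 1 and the PEF is task 2. Judged by video content, the baseline rating may come before the assistant recognises the arm.
- The postintervention rating comes after the whole video, when the arm is known.

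So at least the postintervention SUDS is collected by an unmasked assistant.

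**3. Which listed outcomes pass through the assistant?**
- Primary: PCL-5 (1 instrument). Secondary: S-STAI, T-STAI, PHQ-9 and PANAS (4 instruments). Total 1 + 4 = 5.
- Secondary Outcomes says that outcome measures are completed online through SurveyMonkey. The assistant collects 0 of the 5.
- SUDS is not listed as a primary or secondary outcome, and it appears neither in Hypotheses nor among the outcomes named in Statistical Analyses.
- An indirect route remains: the postintervention S-STAI, a hypothesised outcome, is completed in the same contact in which the assistant plays the video.

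**4. Where does the debriefing fall?**
- Order in Procedure: consent, baseline measures, video, postintervention measures, debriefing; then, 1 month later, the follow-up survey.
- Before the debriefing: postintervention S-STAI and SUDS.
- After the debriefing: S-STAI, T-STAI, PCL-5, PHQ-9 and PANAS at 1 month (Figure 1 legend), that is, 5 of the 5 listed instruments, including the primary.
- Content of the debriefing: not stated.

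The timing is certain. Whether the debriefing reveals the arm or the hypothesis cannot be read from the article.

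**5. Do the labels agree?** Overview says assessor-blinded; the title, abstract, Introduction and Discussion say double-blinded. With self-report only, assessor blinding and participant masking are the same thing for these outcomes. The second party in the double-blinded claim is then the assistant, whose masking fails at step 1.

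**The case against.** The strongest reply is that nothing here reaches the primary outcome as a shown fact. The debriefing may be arm-neutral or confined to support information. Procedure itself says that participants stay blinded throughout, which fits that reading, and debriefing text is something an article normally leaves to the full protocol or ethics file. Both arms receive an active video from the same practitioners with matched tapping and blinking, and the comparison arm never hears of the PEF, so participants could well remain unaware of which video is experimental. The assistant's knowledge bears directly only on SUDS, where the taped instructor asks for the closing rating and the assistant records the participant's number.

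Most of this stands, and it limits the point. The absence of the debriefing text is not in itself a fault. What does not fall away is the contradiction about the assistants, since the article states both the claim and the steps that defeat it, and the fact that a debriefing with no stated safeguard precedes the primary outcome in a trial that promises masking to the end.

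Three stronger readings are tempting but unsupported. A reader might infer that participants are unblinded before month 1; the article does not say so. A reader might take every SUDS rating to be compromised; the baseline rating may precede recognition of the arm. A reader might treat the word flash as what gives the arm away; the article does not say what verbal cue the comparison video uses, so only the PEF and the trauma-only instruction are documented differences.

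**Conclusion.** The stated blinding of research assistants is contradicted by the trial's own procedures. This rests on the text alone and needs no assumption beyond the assistant being able to see or hear what is played on the shared screen. The direct effect is confined to SUDS, at least postintervention, and to the conduct of the first session; none of the five listed outcome instruments is collected by the assistant.

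Participant masking, which is what protects the PCL-5, is at risk but not shown to fail. The risk becomes real only if the debriefing discloses the arm, the comparison or the hypothesis; in that case all five instruments at 1 month are exposed to expectation. No size can be put on such a bias from the documents, and none is claimed.

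The two blinding labels should be reconciled whatever the debriefing says. Severity: should-fix. The documents do not support calling the primary comparison invalid.

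**What to change.** 1. Hold any debriefing content that reveals the arm, the comparison or the hypothesis until the participant has submitted the 1-month survey. Leave support information at the end of session 1 unchanged. If the present statement already discloses none of this, saying so in the article is enough.
2. Have participants enter both SUDS ratings directly in SurveyMonkey rather than report them to the assistant.
3. Replace double-blinded and assessor-blinded, wherever they occur, with one statement: session staff are not masked to the video played, and participants are not told which video is experimental. Use the second half only if the consent form and the Zoom explanation bear it out; the article does not show what either reveals. Correct the sentence in Procedure to match.
4. In Overview and Discussion, do not rest control of placebo response on staff blinding. The matched active comparator and participant masking are the arguments that remain.

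Cost: a small ethics amendment, an added survey item for SUDS, wording changes, a later full debriefing and a less favourable blinding label. Sample size, interventions and analysis model are unaffected.

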#### Comparison Group

Members of the comparison group will be exposed to a pretaped video following similar instructions by the same licensed EMDR practitioners as the experimental group. In a procedure that is identical to the experimental group, participants will be instructed to identify a traumatic event as a target memory. The concept of PEF, however, will not be mentioned, precluding any engagement with or use of it. Instructions will specify that participants should only focus on their traumatic memory and recall as many details as possible. The duration and rhythm of tapping and blinking are identical to what is done with the experimental group, and SUDS measurements are taken in a similar manner. The comparison group protocol will closely follow the S-EMDR format, where clients generate back-and-forth eye movements while focusing on vivid recalls of the traumatic event.

### Outcome Measures

#### Primary Outcome

The primary outcome measure will be the PCL-5 [42]. It is a 20-item self-report instrument measuring the presence and severity of PTSD symptoms. Each item is rated on a 5-point Likert scale ranging from 0 (not at all) to 4 (extremely), indicating how much each symptom has bothered the respondent in the past month. Higher scores indicate more severe PTSD-like symptoms, and a score higher than 31-33 alerts to a possible PTSD diagnosis.

#### Secondary Outcomes

Four self-reported secondary outcome measures will be employed only at baseline and 1-month follow-up. All outcome measures will be carried out on the internet via SurveyMonkey links.

The State-Trait Anxiety Inventory (STAI) Form Y-1 (S-STAI, where S is state subscale) [43] is a 20-item self-report scale that measures subjective tensions, apprehension, nervousness, worries, and physiological arousal. The customary cutoff score for probable clinical levels of anxiety is 40 and above. Trait anxiety is measured by STAI Form Y-2 (T-STAI; trait subscale) [43], which is a 20-item self-report scale. The trait scale measures how people generally feel and it is the most widely used measures for assessing anxiety in clinical and experimental settings [44].

Patient Health Questionnaire-9 (PHQ-9) [45] is used to assess depression levels. This questionnaire has 9 items rated on a 5-point Likert scale from 0 (not at all) to 4 (nearly every day). Similarly, expected ranges for nonminimal, mild, moderate, moderately severe, and severe depression are 0-4, 5-9, 10-14, 15-19, and 20-27.

Positive and Negative Affect Schedule (PANAS) [46] is a 20-item questionnaire that measures positive (10 items) and negative (10 items) affects. Each item is scored with a 5-point Likert scale ranging from 1 (not at all) to 5 (very much). Higher scores on a positive scale translate to higher levels of positive affect, whereas lower scores on negative affect suggest low levels of negative affect. This reliable and valid self-report scale is brief, easily administered, highly internally consistent, and stable at appropriate levels over about as long as a 2-month time period [46]. Visual representation of the study procedures is shown in Figure 1.

**Figure 1 figure1:**

Visual representation of study procedure. Baseline measures: State Subscale-State-Trait Anxiety Inventory (S-STAI), Trait Subscale-STAI (T-STAI), Subjective Units of Distress Scale (SUDS), Posttraumatic Stress Disorder Checklist for DSM-5 (PCL-5), Patient Health Questionnaire-9 (PHQ-9), and Positive and Negative Affect Schedule (PANAS). Postintervention measures: S-STAI and SUDS. Follow-up outcome measures: S-STAI, T-STAI, PCL-5, PHQ-9, and PANAS.

### Hypotheses

FT-EMDR (the experimental condition) will be significantly more effective than S-EMDR in reducing self-report scores on the PCL-5 at 1-month follow-up to the intervention than traditional EMDR.

FT-EMDR (the experimental condition) will be significantly more effective than S-EMDR in reducing self-report scores on the S-STAI at postintervention and 4-week follow-up than traditional EMDR.

FT-EMDR will be significantly more effective than S-EMDR in decreasing self-report scores on the PHQ-9 at 1-month follow-up.

### Statistical Analyses

Statistical analysis will include the calculation of descriptive statistics for demographic and psychological characteristics at baseline, postintervention, and the follow-up period. Study outcomes will be presented as means and SDs for numeric variables and frequencies and percentages for categorical variables. In addition, potential between-group differences at baseline will be evaluated using *t* tests for numeric variables and chi-square tests of independence for categorical variables. Significance will be set at *P*≤.05 and will be presented with *r* values for each questionnaire.

To evaluate the effects of the intervention on primary study outcome (PCL-5) and secondary outcomes (PHQ-9, S-STAI, Trait Subscale-State-Trait Anxiety Inventory, PANAS-Positive, and PANAS-Negative), linear mixed models (LMM) will be employed with an AR (1) covariance structure and random intercepts for each study participant to allow for both fixed and random effects. The LMM assumes that the outcome measure is normally distributed. All models will include adjustments for age and sex (among other psychological characteristics). Statistically significant group×time interactions, indicating between-group changes in outcomes, will be followed by simple main effect evaluation. Cohen d effect sizes for between-group and within-group comparisons will also be calculated according to procedures outlined in Lakens [47]. All analyses will be conducted using RStudio [48] and associated statistical packages, including nlme [49], psych [50], and ggplot2 [51].

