### Sample Size

#### Overview

With the assistance of the Institute for Social Research at York University, the sample size was calculated for a 3-way repeated measures ANOVA. Sample size calculation was conducted using G*Power 3.1.9.4. The options in G*Power 3.1.9.2 were as follows: (1) test family: “*F* test”; (2) statistical test: “ANOVA: Repeated measures, between factor interaction”; and (3) type of power analysis: “A priori: Compute required sample size–given α, power, and effect size.” An a priori power analysis was completed using a moderate effect size (*F*=0.25), 0.8 power (1β error probability), and an α error probability at *P*<.05. G*Power 3.1.9.4 determined that a minimum sample size of 37 participants per group provides ample testing power. Considering a 20% (n=7.4) oversampling to account for potential participant dropout and experimental error, a proposed minimum sample size of 44 per group is deemed adequate to detect within-group and between-group differences based on a repeated measures design.

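### On the usual reading, the primary PCL-5 group×time test compares mean changes; a common baseline mean would make it more precise at no cost, and the two S-STAI contrasts should not wait on an omnibus test

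*Protocol article*

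**What the plan says.** All in the protocol article:

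- **Model (Statistical Analyses).** For PCL-5 and the secondary outcomes, "linear mixed models (LMM) will be employed with an AR (1) covariance structure and random intercepts for each study participant".
- **Covariates (same section).** "All models will include adjustments for age and sex (among other psychological characteristics"). The baseline value of the outcome is not named, and the other characteristics are not listed.
- **Decision rule (same section).** "Statistically significant group×time interactions, indicating between-group changes in outcomes, will be followed by simple main effect evaluation".
- **Measurement times (Figure 1 legend).** All scales are taken at baseline. After that: "Postintervention measures: S-STAI and SUDS. Follow-up outcome measures: S-STAI, T-STAI, PCL-5, PHQ-9, and PANAS". PCL-5 thus has two occasions. S-STAI has three and is the only modelled outcome with a postintervention value.
- **Primary outcome (Abstract, Methods; Hypotheses).** "Primary outcome is PTSD symptoms that are measured by the PTSD Checklist for DSM-5" at 1 month. The hypothesis is superiority "in reducing self-report scores on the PCL-5 at 1-month follow-up to the intervention than traditional EMDR".
- **S-STAI (Hypotheses).** Superiority "in reducing self-report scores on the S-STAI at postintervention and 4-week follow-up than traditional EMDR", which names two time points.
- **Sample Size.** 37 per group before the dropout allowance, from "a moderate effect size (*F*=0.25"), power 0.80 and alpha 0.05. No PCL-5 SD, target difference or correlation between occasions is given.

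**The concern.** A group×time interaction for an outcome with one baseline and one follow-up value exists only if the baseline value is itself a response in the model. If each arm keeps its own baseline mean, which is the conventional form of such a model, the interaction contrasts the two arms' mean changes. Main effects of age and sex leave that contrast as it is. A change score subtracts the baseline in full, whereas the best use of baseline subtracts only the fraction rho. Randomisation makes the true baseline means equal, so the difference between these is pure noise in the primary comparison. In a trial planned around 37 evaluable participants per group, that noise costs power.

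A separate matter arises for S-STAI. Two time-specific hypotheses are stated, but their follow-up tests come only after a significant 2-df interaction.

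**Working it through.** **Plan's own figure.** The only planning figure is 37 per group (74 in total). It cannot be reproduced uniquely, because neither the number of occasions nor rho is stated. With two groups, two occasions and rho 0.5, the G*Power within-between interaction formula gives 34 in total and the between-factors formula gives 97. The between-factors formula reaches 74 at rho about 0.14 with two occasions, or about 0.35 with three. That is a separate matter; 37 is used below only as the evaluable number per arm.

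**Inputs.** n = 37 per arm (Sample Size); two PCL-5 occasions (Figure 1 legend); two-sided alpha 0.05. Assumptions: equal variance σ² at both occasions and in both arms; rho from 0.3 to 0.8; a 0.5 SD difference at 1 month. A between-group f of 0.25 with two groups corresponds to d = 2 × 0.25 = 0.5.

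**Variance of the group contrast, complete data.**
- Free baseline means (difference in mean change): (2/n) × 2σ²(1−rho).
- Common baseline mean: (2/n) × σ²(1−rho²).
- Ratio: (1−rho²) / [2(1−rho)] = (1+rho)/2.

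At rho 0.5, in SD units, the standard errors are √(2×1.00/37) = 0.2325 and √(2×0.75/37) = 0.2013. The ratio of 0.75 is worth 1/0.75 = 1.33 times the participants.

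**Variance ratio with a fraction p followed up.** The mixed model uses all baselines. Per arm, the free-baseline variance is σ²[(1−rho²)/(pn) + (1−rho)²/n] and the constrained variance is σ²(1−rho²)/(pn). The ratio is (1+rho) / [(1+rho) + p(1−rho)]. At p = 0.8 and rho 0.5 it is 1.5/(1.5+0.4) = 0.79.

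**Power.** Noncentral t, 72 df, n = 37 per arm, complete data, assumed 0.5 SD:

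| rho | ratio, complete | ratio, 20% lost | power, free baseline | power, common baseline |
|---|---|---|---|---|
| 0.3 | 0.65 | 0.70 | 0.43 | 0.60 |
| 0.5 | 0.75 | 0.79 | 0.56 | 0.69 |
| 0.7 | 0.85 | 0.88 | 0.78 | 0.84 |
| 0.8 | 0.90 | 0.92 | 0.92 | 0.94 |

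**Check that the interaction is the change score.** In one simulated complete data set (37 per arm, age and sex adjusted), the mixed-model interaction was −0.43616 (SE 0.2056) and the difference in mean change −0.43616 (SE 0.2055). With a common baseline mean the SE was 0.178. With 15 follow-ups removed, the interaction (−0.466) and the completers' change difference (−0.435) no longer coincided, so the identity is exact only with complete data.

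**S-STAI.** Three occasions give a 2-df interaction. In simulation (rho 0.5, 37 per arm, 0.5 SD at both later visits), each between-group test had power of about 0.56 to 0.57 alone, and 0.37 to 0.38 when a significant interaction was required first. With the effect at postintervention only, the figures were 0.57 and 0.43. These are tests at a single visit without baseline adjustment.

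**The case against.** **The planned test is valid.** Under randomisation the interaction is a standard and unbiased comparison, and the hypothesis is worded as a reduction in score, which a difference in change addresses. This stands: the loss is of precision only.

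**Free baseline means are inferred.** The article does not say how baseline enters, and the unnamed psychological characteristics might include a baseline score. This stands as a caveat. Free means remain the conventional reading, and a baseline PCL-5 that served as both response and covariate in one model would itself need explaining.

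**The size rests on assumptions.** This also stands. If f = 0.25 is read as the two-occasion within-between interaction, it means a 4 × 0.25 = 1.0 SD difference in change. The planned test then already has power 0.95 at rho 0.3 and 0.99 at rho 0.5, and the constraint adds at most about 5 points.

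**The gate may look as if it covers the primary outcome.** A reader might infer that the 1-month PCL-5 comparison, or a postintervention one, is examined only after an omnibus test. The document does not support that. PCL-5 has no postintervention value, and its interaction has 1 df and is itself the between-group test of change to 1 month. Only the follow-on simple effects are conditional.

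**For S-STAI the gate has a purpose.** An omnibus test gives some protection against multiplicity, and the planned means, SDs and Cohen d are not conditional on it. Both points are fair. What is withheld is the formal test of two contrasts that the Hypotheses section names in advance.

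**Conclusion.** The point holds as one of efficiency, and the change should be made. On the conventional reading, the primary PCL-5 analysis gives up 15% to 35% of the variance at rho 0.7 to 0.3 with complete data, or about 12% to 30% with 20% lost at follow-up. For an assumed 0.5 SD difference and 37 per group with complete data, that is between 6 and 17 percentage points of power. At rho 0.8 it is about 2 points, and for a much larger effect it matters little. The variance ratios rest on assumed rho, equal variances and free baseline means; the power figures also rest on the assumed 0.5 SD difference. Nothing here shows bias or an invalid test. The gating point is confined to S-STAI, a secondary outcome.

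**What to change.** In Statistical Analyses, specify the mixed model with one baseline mean common to both arms: terms for visit and for group × post-baseline visit, adjusted for age and sex. Name the 1-df group contrast in PCL-5 at 1 month, with its 95% CI, as the primary test. Use the same form for the other outcomes.

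ANCOVA of the 1-month score on baseline is the same analysis only with complete data. The constrained mixed model is preferable because it keeps participants who miss follow-up.

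For S-STAI, state that the postintervention and 1-month 1-df contrasts will be reported with 95% CIs whatever the 2-df interaction shows, and label them as secondary.

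The cost is a few sentences and a small change in the model code, with no new data. The common baseline mean relies only on randomisation. The change should be fixed before any unblinded analysis.
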